### Intervention

The Fatigue, Learning, and Memory Enrichment (‘FLaME’) program was developed by members of the research team by incorporating strategies that have been trialled and found successful in fatigue
^
21–
23
^ and cognitive rehabilitation
^
14,
15,
24–
28
^ interventions for children. Strategies for cognitive fatigue include pacing, activity scheduling and monitoring, behavioural strategies to regulate stress, and basic psychoeducation (e.g., sleep hygiene). Strategies for cognition focus on regulating attention to information and optimising encoding and retrieval (e.g. chunking and elaborative semantic encoding strategies such as the PQRST method and mnemonics), age-appropriate problem-solving strategies, and compensatory strategies such as visual reminders. A paediatric neurocognitive interventions model (PNI model
^
24
^) informed the theoretical development of the intervention. In the PNI model, skills are targeted sequentially based on a developmental hierarchical model where foundational factors (e.g., psychosocial needs) are addressed first, followed by adult-supported compensatory strategies, with independent use of strategies for specific impairments delivered only once these earlier levels have been addressed. This approach was recently piloted to deliver strategy-based rehabilitation for memory impairment in children with paediatric traumatic brain injury, finding large effect sizes for improvements in everyday memory difficulties
^
29
^. Extending the PNI model for childhood brain tumour, cognitive fatigue is a common co-occurring difficulty that plausibly benefits from intervention at the foundation stage before subsequent levels of cognitive rehabilitation are delivered.

All interventional components are delivered by a Psychologist under the supervision of a senior Clinical Psychologist & Neuropsychologist. The full intervention is delivered over 12 weeks, inclusive of 10, 1-hour individual sessions (child and parent attends) and a separate parent and peer psychoeducational group session during each block (i.e. during the fatigue and cognitive intervention blocks). The group sessions reinforce the same psychoeducational components of individual sessions and are primarily to facilitate peer support. The cognitive rehabilitation-only intervention is delivered in a 6-week block consisting of 6 individual sessions (child and parent attends) and a parent and peer group session. Psychoeducational webinars for each block of cognitive fatigue and cognitive rehabilitation are provided to the child’s teacher/Special Educational Needs Co-ordinator (SENCo) to enhance systemic support and maximise generalisation of strategies. The intervention is delivered hierarchically with cognitive fatigue management introduced first (in the full intervention), followed by cognitive rehabilitation strategies with consideration to developmental stage of the child. The programme content and concepts (e.g., PQRST, chunking, pacing) per session are consistent across age groups, but the delivery (e.g., wording, supporting images, and consolidation activities) is adapted by age. Degree of involvement of an adult in intervention activities can be adapted according to the child’s level of development and independence.

The intervention can be delivered in face-to-face or remote format depending on participant preference. Meta-analysis
^
30
^ and review
^
31
^ of similar remote skills-based neuropsychological interventions for young people with diverse neurological conditions have recently found remotely delivered interventions have high levels of feasibility and acceptability without compromise to fidelity and efficacy. They also have the advantage of greater geographical reach and access for families who may otherwise be unable to participate
^
15,
32
^. Criteria for discontinuing the intervention includes patient request, disease relapse requiring urgent medical treatment, and where the participant becomes ineligible based on the eligibility criteria.

### Study data and outcome measures

**
*Demographic and clinical data*
**

Demographic data: age, date of most recent neuropsychological assessment, sex, ethnicity, living location, parental education and occupation.Clinical data: primary oncology diagnosis/tumour type, tumour location, tumour WHO grade, oncology treatment type (surgery, chemotherapy, and/or radiotherapy), co-morbid health conditions, diagnoses, and treatments.

**
*Neuropsychological assessment data*
**

All children will have received protocol-based neuropsychological assessment/consultation within the clinical service prior to commencing the intervention. This includes standardised measures such as direct measures of intellectual function (e.g., Wechsler Intelligence Scale for Children – 5th Edition), attention (e.g., Conners Continuous Performance Task – 3d Edition), memory (e.g., Children’s Memory Scale), and indirect measures of everyday skills (e.g., Adaptive Behaviour Assessment – 3rd Edition, Behaviour Rating Inventory of Executive Function – 2nd Edition). Specific measures are administered according to the age of the child and presenting needs (see
https://doi.org/10.6084/m9.figshare.29376176 for a typical neurocognitive assessment battery for paediatric neuro-oncology in the service). This takes place as part of standard care and will be used to characterise the cognitive needs of the participant sample.

**
*Feasibility measures*
**

**Demand**

1. Acceptance/refusal rates for potentially eligible participants.2. Documentation of ineligibility and refusal reasons.3. The completed number of sessions out of the total planned and attrition rate across the lifecycle of the study.4. Record of any bias in dropout (i.e. by demographic and clinical characteristics).5. Length of time to recruit participants within the study recruitment window.6. A qualitative logbook of any unanticipated challenges or ‘lessons learned’.

**Implementation, practicality, adaptation, and integration**

1. Fidelity: Clinician and observer report of fidelity using a checklist for the content coverage of the specific intervention session.2. Participant adherence: Adherence to intervention strategies through completion rate of a brief home learning task related to the individual session content of the week. Adherence will also be discussed at post-intervention interviews.3. Estimated cost analysis of resource required for the RCT and/or sustainability in the organisation.4. Feasibility of data collection time points as indicated by attrition, missing, and unusable data.5. Documentation of obstacles to recruitment in the organisation.6. Mode of intervention delivery.

**
*Acceptability measures*
**

The study will triangulate qualitative and quantitative data through TFA-informed questionnaire
^
19
^ and qualitative interviews. The TFA-questionnaires were developed for the study using a published template
^
19
^ as a session-by-session and post-intervention measure for each trial arm. Questionnaires were adapted according to the age of the child. Semi-structured interview schedules were also developed for children, parents/carers, and therapists delivering the intervention using the same template and research
^
33
^. The questionnaires and interview guides were independently evaluated by two researchers with advanced experience in psychometrics for paediatric health. To assess the construct validity of each item a process of ‘back coding’
^
33,
34
^ was employed. Each researcher was sent the questionnaire and interview schedule items in a random order with a list of TFA constructs and were required to match each question to the correct construct and rate their confidence on a five-point scale (1=not at all confident, 5 = completely confident). This process indicated strong construct validity where 95% of items were correctly matched to their construct with a high degree of certainty (average 5 of 5 for each construct across both researchers). The only items not correctly matched on one occasion and by one researcher were the ‘affective attitude’ and ‘general acceptability’ items which were interchanged. A second researcher rated certainty of 4 out of 5 for the ‘affective attitude’ and ‘general acceptability’ items of the questionnaires, where all other items yielded certainty of 5/5 across all questionnaires and interviews. On discussion with the researchers, it was agreed that these two items had a high degree of conceptual overlap in questionnaire format and would likely be highly correlated. A decision was made to eliminate the general acceptability item from the questionnaires which is an optional item
^
19
^. The item was retained for the interviews however where it was a more distinct and could be explored with prompt questions.

The following TFA-measures will be used:

1. Session-by-session TFA-Questionnaire for parents & child.2. Post-intervention or standard care TFA-Questionnaire for parents & child.3. TFA-informed qualitative interview with participants on experience and acceptability of intervention or standard care, and acceptability of randomisation.4. Post-intervention TFA-Questionnaire with qualitative feedback for education staff.5. Post-intervention feasibility and acceptability interview with the therapist delivering the intervention.

The Satisfaction Questionnaire after Cognitive Skills Training Interventions – parent
^
15
^ will be used as a comparison to another published study.

**
*Preliminary outcome measures*
**

The inclusion of outcome measures in the feasibility trial is for ‘limited-efficacy testing’ to inform a future fully powered RCT and for descriptive analysis of patient benefit by assessing 1) the measures’ sensitivity to change in the PBT population within the context of a feasibility trial, and 2) to estimate effect sizes of the measures
^
35
^. Outcome measures are administered at baseline, week 6, and weeks 12–14 before acceptability interviews (see
Figure 1: Study Flowchart):

1. Fatigue measuresa. Primary outcome measure: Goal Based Outcome (GBO) for management of cognitive fatigue - parent & child
^
36
^
b. Secondary outcome measures: Multidimensional Fatigue Scale – parent and child
^
37
^, individual daily fatigue analogue scale (child), % school attendance (from school report)2. Cognitive measuresa. Primary outcome measure: GBO for management of cognitive difficulty – parent and child
^
36
^.b. Secondary outcome measures: Behaviour Rating Inventory of Executive Function – second edition (BRIEF-II) – parent and teacher, PedsQL Core + Brain Tumour Cognitive Problems module – child and parent
^
38
^, The Brief Illness Perceptions Questionnaire – child
^
39
^

These outcomes measures were selected due to their psychometric properties, suitability to the aims of strategy-based cognitive rehabilitation, and precedence and sensitivity to detecting change after rehabilitation interventions
^
22,
29,
40–
44
^. The MDFS was selected as an outcome measure for cognitive fatigue as it is the only fatigue measure that compartmentalises fatigue into subdomains. In our clinical experience of this population, sequelae of cognitive fatigue are often reflected across the domains of the MDFS (e.g., problems starting and finishing activities, feeling tired or napping after cognitive activities) but with higher scores within the cognitive domain. We will evaluate this profile in the final sample to inform if and how this measure should be used in an RCT. Where measures are protected by copyright (PedsQL Multidimensional Fatigue Scale, Core module, and Brain Tumour module, and the BRIEF-II) the appropriate license agreement has been obtained for use within the study.

### Participant timeline

A schedule of participant procedures is shown in
Table 1.

**Table 1. T1:** Schedule of Participant Procedures Key: A = Arm A (Full intervention), B = Arm B (Cognitive rehabilitation only), C = Arm C (Standard care)

Procedure	Screening	Baseline	Wk1	Wk2	Wk3	Wk4	Wk5	Wk6	Wk7	Wk8	Wk9	Wk10	Wk11	Wk12	12–14
Informed consent	A,B,C														
Collect demographics	A,B,C														
Collect clinical information	A,B,C														
Full eligibility screen	A,B,C														
GBO for fatigue		A,B,C	Arms A & B at each 1:1 intervention session					A,B,C	Arms A at each 1:1 intervention session						A,B.C
MDFS		A,B,C						A,B,C							A,B.C
Fatigue VAS		A,B,C	A,B	A,B	A,B	A,B	A,B	A,B,C	A	A	A	A	A	A	A,B.C
School attendance %		A,B,C													A,B.C
GBO for cognition		A,B,C	Arms A & B at each intervention session					A,B.C	Arms A at each intervention session						A,B.C
BRIEF II		A,B,C						A,B,C							A,B.C
PedsQL core & BT modules		A,B,C						A,B,C							A,B.C
BIPQ		A,B,C						A.B.C							A,B.C
Group intervention session			Arm A & B 1 x session						Arm A = 1 session						
Individual intervention session			Arm A = 4 x sessions, Arm B = 6 sessions						Arm A = 6 sessions						
TFA sessional measure			Arms A & B at each intervention						Arms A at each intervention session						
TFA post intervention questionnaire								B							A/C
Satisfaction with Cognitive Skills Training Questionnaire								B							A
TFA interview															A,B,C

GBO=Goal Based Outcome, MDFS=PedsQL Multidimensional Fatigue Scale, VAS=Visual analogue scale, BRIEF II=Behaviour Rating Inventory of Executive Function second edition, PedsQL=Pediatric Quality of Life Inventory, BT=Brain Tumour, BIPQ=Brief Illness Perceptions Questionnaire, TFA=Theoretical Framework for Acceptability

### Data recording, storage, and access

A Case Report Form (CRF) will be assigned for all participants entering the study. The CRF will be depersonalised and the participant and CRF will be assigned an anonymised code (Patient Identification Number; PID). All data recorded will meet the standards set out by the Sponsor’s local policies. An electronic Study Site File will be maintained on a secured GOSH Trust drive which will only be accessible to members of the research team at GOSH. All study source data (e.g., from patient records and study measures) will be documented in the electronic CRF. No data fields will be left blank. Where there is missing data, this will be coded with a pre-specified key. All data from the CRF will be transferred to an electronic study file in depersonalised format when the participant completes the study. The CRFs and study file will be held in duplicate in a secure GOSH Trust drive and Trust approved encrypted storage device and only accessible to the GOSH site research team. Where data is transferred from source data to CRFs, and from the CRF to study file, this will be checked for accuracy by a second member of staff (named in the CRF). The Chief Investigator (CI) or delegated individual from the research team will perform random regular audit of CRFs and the study file for accuracy (checking a minimum of a randomly identified 15%). 

### Data processing and analyses

**
*Quantitative data*
**

A detailed statistical analysis plan will be produced prior to data analyses. All demographic, clinical, and neuropsychological assessment data will be summarised by group. Quantitative feasibility data will also be summarised for the sample. Quantitative data from TFA-questionnaires will also be used to compare and rank individual intervention sessions, the overall intervention, and compare to acceptability measures in the standard care arm. Means and standard deviations (or alternative as appropriate) for the satisfaction questionnaire will be described according to intervention arm.

Statistical analyses will mainly focus on change detected in the outcome measures (e.g., GBO, PedsQL, BRIEF-II). Means and standard deviations (or equivalent) will be described for the outcome measures for each group at each time point (baseline, week 6, and weeks 12–14), and compared using repeated measures ANOVA to address these two aspects of limited efficacy testing. The focus of the statistical analyses will be to estimate effect sizes (e.g., partial eta squared, Cohen’s d, or non-parametric equivalents as needed) for each measure. Effect sizes will then be ranked across the outcome measures to determine which is most sensitive to change to inform the future clinical trial. The 95% confidence intervals for the effect sizes will also be considered.

**
*Qualitative data*
**

Qualitative data generated by feasibility outcomes will be grouped into themes. Frequency rates for each theme will be calculated if this is appropriate. It will be used to accompany description of quantitative feasibility data.

The primary qualitative data will be generated by the TFA-informed interviews. This data will be analysed using thematic analysis
^
45
^, an analytic method that explores patterns and themes in qualitative data. Themes will be analysed according to the TFA. The final analyses will be shared with two participants to provide a member check of final themes and discussed with the Patient and Public Involvement Advisory Group.

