**Figure 1. f1:**
[figure not shown]
Study Flowchart.

Thirty-six participants will be recruited and randomised to either 1) a 12-week block of intervention (cognitive rehabilitation with fatigue management), 2) a 6-week block of intervention (cognitive rehabilitation alone), or 3) 12 weeks of standard care. Randomisation will be undertaken centrally by the study team using GraphPad random assignment. Participants will be young people aged 7 years to 17 years, 11 months who have been diagnosed with a childhood central nervous system (CNS; brain) tumour, or received oncology treatment to the brain, and are current patients at Great Ormond Street Hospital for Children (GOSH). The study is a single-site study. All participants will be recruited at GOSH, with each participant completing a 14-week study period. All study procedures will take place at GOSH. Standard care at the study site consists of 1) a single feedback session on the neuropsychological assessment findings and recommendations, and 2) continuation of routine oncology medical care, as appropriate for the patient, without any neuropsychological intervention.

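### The repeated measures ANOVA puts all arms on one clock although their treatment blocks are offset, so the effect sizes to be ranked mix treatment effect with stage of treatment

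*Protocol article*

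**What the plan says.** Study design and setting gives arm A "a 12-week block of intervention (cognitive rehabilitation with fatigue management") and arm B "a 6-week block of intervention (cognitive rehabilitation alone"); arm C has 12 weeks of standard care. Under Intervention, the full programme is delivered "with cognitive fatigue management introduced first (in the full intervention), followed by cognitive rehabilitation strategies", and "The full intervention is delivered over 12 weeks, inclusive of 10, 1-hour individual sessions". For arm B, "The cognitive rehabilitation-only intervention is delivered in a 6-week block consisting of 6 individual sessions". In Table 1 the row for individual sessions reads "Arm A = 4 x sessions, Arm B = 6 sessions" in the first half of the schedule, and gives 6 sessions to arm A only in the second half.

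Outcomes are taken in all three arms at baseline, week 6 and weeks 12–14. Data processing and analyses, under quantitative data, has the groups described "at each time point (baseline, week 6, and weeks 12–14), and compared using repeated measures ANOVA". It gives partial eta squared and Cohen's d as example effect sizes and says that effect sizes will be ranked across measures to find the one most sensitive to change. It does not link any visit to a stage of treatment.

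Table 1 places the post-intervention acceptability and satisfaction questionnaires at week 6 for arm B and at weeks 12–14 for arm A. The acceptability interview is at weeks 12–14 for every arm.

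**The concern.** Arms A and B receive the same kind of cognitive block, but arm A receives it one block later. On a cognitive outcome, neither post-baseline visit sees the two arms at the same stage. Week 6 sets an arm that has not begun cognitive rehabilitation against one that has finished it. The last visit sets an arm that has just finished against one that finished well before.

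Two uses of the results are exposed. The first is the sensitivity ranking (objective 4). A group-by-time effect size grows or shrinks with the arrangement of the blocks, and it does so differently for cognitive and fatigue measures, so the ranking can reflect the timetable as well as responsiveness. The second is any reading of A against B on benefit. The background section says the study will determine whether adding fatigue management improves patient-reported benefit as well as feasibility and acceptability.

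**Working it through.** **1. Timeline (figures from Intervention and Table 1).** The session counts agree: 4 + 6 = 10 individual sessions in arm A.

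| Visit | Arm A | Arm B |
|---|---|---|
| Week 6, cognitive sessions received | 0 of 6 | 6 of 6 |
| Weeks 12–14, weeks since treatment ended | 12 − 12 = 0 to 14 − 12 = 2 | 12 − 6 = 6 to 14 − 6 = 8 |

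That arm A's first 4 sessions all belong to the fatigue block is an inference. It follows from the stated order, from the description of separate fatigue and cognitive blocks, and from the match between arm A's later 6 sessions and arm B's 6-session block. Nothing in the protocol contradicts it.

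**2. Same-visit A v B contrast on a cognitive measure.** Assumptions, none from the protocol: both arms gain the same effect d by the end of their own cognitive block, the fatigue block does not move the measure, and arm B loses a fraction r by weeks 12–14.

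- Week 6: A − B = 0 − d = −d, whatever r is.
- Weeks 12–14: A − B = d − d(1 − r) = rd.

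With d = 0.5 SD and r = 0.5 these are −0.5 SD and +0.25 SD, although the true difference at equal stage is 0. The week-6 gap needs no fading assumption. The later one is 0 without fading and changes sign if arm B continues to improve.

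**3. How often the interaction would signal a difference.** Simulated A v B group-by-time ANOVA with 12 per arm, three visits, SD 1, within-person correlation 0.5, r from 0 to 0.5 and 4,000 runs per setting:

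| True d, equal in both arms | Mean partial eta squared | Significant at 5% |
|---|---|---|
| 0 | about 0.04 | about 5% |
| 0.5 | 0.08–0.11 | 21–36% |
| 0.8 | 0.14–0.20 | 49–75% |

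When each arm's change is taken from baseline to the end of its own cognitive block, the figures return to about 0.04 and about 5%. That aligned version assumes no time trend, which is why the fix goes through arm C.

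**4. Effect on the ranking.** Take three-arm mean profiles over baseline, week 6 and weeks 12–14, with no fading and no change in arm C. The interaction sum of squares is the sum over the nine cells of (cell − row mean − column mean + grand mean)².

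- Cognitive measure, offset blocks: A = (0, 0, d), B = (0, d, d), C = (0, 0, 0). Six cells are ±d/3 and three are 0, so the sum is 6d²/9 = 0.67d².
- Cognitive measure, if both arms had received the block in weeks 1–6: A = B = (0, d, d), C = (0, 0, 0). The sum is (12 + 24)d²/81 = 0.44d².
- Fatigue measure moved only by arm A's first block and maintained: A = (0, d, d), B = C = (0, 0, 0). The sum is (24 + 12)d²/81 = 0.44d².

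A cognitive and a fatigue measure with the same end-of-block effect d would differ by a factor 0.67/0.44 = 1.5 in the quantity behind partial eta squared. Setting the first two cases side by side shows that the excess comes from the offset and not from two arms responding instead of one.

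**5. Price of a stage-aligned A v B comparison through arm C.** The estimate is (A − C at weeks 12–14) − (B − C at week 6). Assume equal variance σ², n per arm and within-person correlation ρ. Using follow-up means, the variance is [1 + 1 + 2(1 − ρ)]σ²/n, against 2σ²/n for the direct same-visit contrast. At ρ = 0.5 this is 3 against 2, so the SE is √1.5 = 1.22 times as large. Change from baseline gives the same ratio. With covariate adjustment for baseline the variances are 2(1 − ρ²) + 2(1 − ρ) = 2.5 against 2(1 − ρ²) = 1.5, a ratio of √1.67 = 1.29.

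**The case against.** The analysis section does not name the omnibus interaction or an A v B contrast as its estimate. Cohen's d is usually pairwise, a detailed analysis plan is promised, and nothing written rules out stage-labelled contrasts. This stands in part: the three common visits and the test are fixed, the ranking depends on the resulting effect sizes, and followed as written they carry the offset. Choosing the contrasts by stage is a better method for that stated purpose and not merely a missing detail.

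The efficacy objective (objective 3) is against standard care. Arm C is measured at both follow-up visits, so A v C and B v C at any one visit are concurrent randomised comparisons. This stands in full.

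The choice of arm is tied to feasibility and acceptability (objective 2), and the acceptability and satisfaction questionnaires already follow each arm's end of treatment. The session-by-session acceptability measure and goal ratings in arms A and B add further stage-specific data. This also stands. A reader might infer that the choice of arm is itself confounded, or that the efficacy comparison is invalid; the documents support neither.

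No analysis can match a 6-week and a 12-week programme on both stage and time since baseline, and the indirect comparison is less precise. This stands, and is why the direct comparison should be kept.

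Moving arm B's interview to week 6 is tempting, but it would come before that arm's final outcome measures, whereas the protocol places outcomes before interviews. That is a trade-off and not an error.

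**Conclusion.** The point holds in a limited form. The offset is documented, and the planned common-visit ANOVA makes no allowance for it. An overall group-by-time effect size, and a same-visit A v B contrast on cognitive outcomes, would mix treatment effect with stage of treatment, which can distort the sensitivity ranking and any A v B reading of benefit.

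The size is illustrative. The effects of 0.5 and 0.8 SD, the fading of 0–50%, the correlation of 0.5 and the absence of a fatigue-block effect on cognition are assumptions. The week-6 distortion does not depend on fading, but it would be smaller if fatigue management itself improved the cognitive measures. The same-visit A v B contrast is not wrong in itself: it compares whole strategies from randomisation, and misleads only if read as a comparison of the programmes at equal stage. The consequence is moderate, because this is limited-efficacy testing in a feasibility study. The sample size of 36 (3 × 12) rests on a rule of thumb and is unaffected.

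**What to change.** In the quantitative analysis text, base the effect sizes used for ranking on baseline-adjusted contrasts with concurrent standard care, each with its 95% confidence interval and labelled by stage:

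- B v C at week 6, and A v C at weeks 12–14: end-of-intervention effects.
- A v C at week 6: fatigue-block effect.
- B v C at weeks 12–14: maintenance.

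Rank measures within a stage label, not across labels. Keep the same-visit A v B comparison and call it a whole-strategy comparison from randomisation. Report any stage-aligned A v B comparison through arm C beside it, noting its lower precision (SE about 22% larger at a within-person correlation of 0.5, and about 29% with covariate adjustment for baseline) and the different time since baseline.

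Leave the interview schedule as it is, and report arm B's 6–8 week recall lag as a limitation.

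The cost is wording in the protocol or analysis plan. No visit, measure or participant is added, since arm C already contributes data at both visits.

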^ with a paucity of research and poor feasibility and acceptability of trialled interventions. Drill-based computerised rehabilitation has been the focus of the small number of available studies, however, the feasibility and acceptability of this approach for PBT is low
^
12
^ and has well documented problems in poor generalisation to skills beyond the trained task (e.g., academic skills) and poor maintenance of improvements
^
13
^. The focus of drill-based interventions is typically to remediate specific cognitive deficits which can neglect the broader profile of multiple co-occurring neuropsychological difficulties common after PBT.

Rehabilitation in paediatric acquired brain injury has greatest potential when it includes internal and metacognitive strategy-use, is adapted for developmental level, and delivered within a systemic context
^
10
^. There is currently one good quality randomised controlled trial (RCT) of a cognitive rehabilitation intervention that incorporates strategy-use for PBT
^
14
^. The intervention resulted in improvements in parental report of child inattention and academic attainments, albeit with small effect sizes. The program involved strategy-use training, but also included a demanding drill-based practice component (requiring 40 hours of practice), with only 60% of participants completing the intervention. A subsequent study
^
15
^ omitted the drill-based practice and extended the strategy-use component (15 sessions, 20 hours in total), combining it with systemic support in a smaller pilot study. The power and generalisability of the findings are limited by a small sample size, however significant improvement for written expression was found along with trends towards improvement on neurocognitive measures. Participants also rated high levels of satisfaction, particularly because the intervention improved their understanding of their cognitive strengths and weakness.

Despite some promising findings for strategy-based cognitive rehabilitation, poor feasibility is reflected in generally low completion rates. Cognitive fatigue (extreme mental tiredness) is one of the most frequently reported and distressing chronic symptoms after PBT
^
16

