The justification for the sample size comes from the NIHR Research Design Service (RDS) London evidence for sample sizes for feasibility studies (
https://www.rds-london.nihr.ac.uk/resources/justify-sample-size-for-a-feasibility-study/) and associated evidence for estimating a standard deviation to power the future definitive trial. There is no formal way to power a standard deviation estimate which is a measure of variability, therefore various rules of thumb have been developed that the sample size for a feasibility trial should be between 24–50
^
46,
47
^. A sample size of 36 (12 participants per arm of the study) is further justified by the feasibility and the precision this provides in estimating the mean and the variance
^
46
^. This can then be used to calculate power for a more precise hypothesis for a definitive randomised controlled trial.

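### Repeated measures ANOVA with baseline as a time point gives less precise arm effect sizes than a baseline-adjusted mixed model, and in its classical form omits any child who misses a visit

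*Protocol article*

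**What the plan says.** The Quantitative data part of Data processing and analyses describes means and SDs "for each group at each time point (baseline, week 6, and weeks 12–14"), and these are to be "compared using repeated measures ANOVA to address these two aspects of limited efficacy testing". The resulting effect sizes are then ranked across measures to find the one most sensitive to change. On precision the plan adds: "The 95% confidence intervals for the effect sizes will also be considered".

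Under Preliminary outcome measures the schedule is: "Outcome measures are administered at baseline, week 6, and weeks 12–14 before acceptability interviews". Table 1 departs from this for one measure: school attendance is collected at baseline and weeks 12–14 only.

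On numbers, Sampling and sample size gives "A sample size of 36 (12 participants per arm of the study") and rests it on rules of thumb: "various rules of thumb have been developed that the sample size for a feasibility trial should be between 24–50". No allowance for dropout is stated. Incomplete data are foreseen as a feasibility measure: "Feasibility of data collection time points as indicated by attrition, missing, and unusable data". On handling them, Data recording, storage, and access says only that missing values will be coded. A detailed SAP is promised before analysis, but the method of comparison is already named in the protocol.

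**The concern.** Two properties of the named method matter in a trial this small.

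- **Missing visits.** Classical repeated measures ANOVA needs every level of the repeated factor. A child with no week 6 value for a measure is lost for that measure, even with baseline and final values in hand.
- **Baseline as an outcome.** With baseline as a level of time, the arm effect sits in the arm-by-time term, which contrasts changes from baseline. A change score carries the full noise of the baseline measurement. Using baseline as a covariate removes only the part that predicts the outcome, and is more precise for any r below 1.

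At stake are the effect sizes, their 95% confidence intervals and the ranking built on them, which is meant to guide the choice of outcome for the definitive RCT. If missing visits are related to fatigue, the children with complete data would also be a selected group; the documents do not allow the size or direction of that to be judged.

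**Working it through.** **Inputs.** From the protocol: 3 arms × 12 = 36, which reproduces the stated total; three visits; 95% intervals. There is no power calculation to reproduce. Not in the protocol, so assumed: the correlation r between baseline and follow-up (0.5–0.8), equal SDs across visits, and the missing rate per visit (10–20%).

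**Step 1: cost of using change.** In units of the outcome variance, with n children per arm:

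- change-score contrast: variance = 2(1−r) × 2/n
- baseline-adjusted contrast: variance = (1−r²) × 2/n
- ratio, adjusted to change: (1−r²) / [2(1−r)] = (1+r)/2

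Estimating the baseline slope costs a factor of about 1 + 1/31 = 32/31 (36 − 3 = 33 residual degrees of freedom, less 2).

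| r | 2(1−r) | 1−r² | Ratio | Reduction | Ratio × 32/31 | Reduction |
|---|---|---|---|---|---|---|
| 0.5 | 1.00 | 0.75 | 0.75 | 25% | 0.774 | 22.6% |
| 0.6 | 0.80 | 0.64 | 0.80 | 20% | 0.826 | 17.4% |
| 0.7 | 0.60 | 0.51 | 0.85 | 15% | 0.877 | 12.3% |
| 0.8 | 0.40 | 0.36 | 0.90 | 10% | 0.929 | 7.1% |

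With all 12 per arm observed, the 95% half-width for a difference between two arms, penalty included, falls from 0.83 to 0.73 SD at r = 0.5, and from 0.64 to 0.60 SD at r = 0.7.

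**Step 2: cost of dropping incomplete children.** If each of the two post-baseline visits is missed independently with probability p, complete cases = 36(1−p)² and children with a final value = 36(1−p).

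- p = 10%: 36 × 0.81 = 29.2 complete; 32.4 with a final value
- p = 20%: 36 × 0.64 = 23.0 complete; 28.8 with a final value

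Under monotone dropout (nobody returns after a missed visit), every child with a final value also has week 6. The complete cases are then exactly the children with a final value, and the gain is essentially that of Step 1, plus a little recovered from week 6 data.

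**Step 3: both together.** A simulation (600 runs per setting, 12 per arm, equal correlation between visits, independent missingness) compared the complete-case change contrast with a likelihood-based model having a common baseline mean. Variance ratios, change to likelihood-based:

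- 10% missing per visit: 1.42 (r = 0.5) and 1.21 (r = 0.7), i.e. reductions of 1 − 1/1.42 = 30% and 1 − 1/1.21 = 17%
- 20% missing per visit: 1.65 and 1.48, i.e. reductions of 39% and 32%

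These carry simulation error. With nothing missing the runs gave 1.40 and 1.15, against 1/0.774 = 1.29 and 1/0.877 = 1.14 from Step 1. They indicate the order of size only.

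**Step 4: school attendance.** Table 1 has two time points for it, so the three-point comparison cannot be fitted to this measure.

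**The case against.** The strongest reply is that a SAP is to come and that missing-data handling and covariates normally belong there. That stands for anything the protocol leaves open: it nowhere prescribes a complete-case analysis, so the loss of children follows from the usual form of the named method, not from a stated rule. It does not answer the choice of method, which the protocol fixes.

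Three stronger readings are tempting, and the documents do not support them.

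- *The SDs for the definitive trial would come from completers only.* The protocol describes SDs for each group at each visit, which needs no complete set of three. The 24–50 rule of thumb concerns estimating an SD, so a complete-case count of 23 does not breach it.
- *Only about 22 of 36 children would remain.* This applies 60% to 36 (21.6). The protocol's words about an earlier RCT are "with only 60% of participants completing the intervention": that is completion of an intervention requiring 40 hours of drill practice, not attendance at outcome visits. The present intervention has 6 or 10 one-hour sessions, and the standard-care arm has none to complete.
- *The combined loss is known to be 28–36%.* That figure follows if 15% miss week 6 and 25% independently miss the final visit: 12 × 0.85 × 0.75 = 7.65 complete per arm against 9 with a final value, so 0.85 × 7.65/9 = 0.72 at r = 0.7 and 0.75 × 7.65/9 = 0.64 at r = 0.5. With the same rates and monotone dropout it shrinks to 15–25%.

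It can also be said that baseline as a level suits the stated aim of assessing sensitivity to change. That is fair, and the fix must keep within-arm change. School attendance is one secondary measure, and a two-level ANOVA could be run on it, so on its own that is a wording point.

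**Conclusion.** The concern holds as a matter of efficiency and of which children are used. The named method estimates arm effects with more variance than the same data allow: by the formula, adjustment lowers it by 15–25% for r = 0.7–0.5, by about 12–23% after the small-sample penalty, and by 7–10% at r = 0.8. Intermittent missing visits add a further loss; monotone dropout adds little. All of this rests on assumed correlations and missing rates, and on the classical form of the ANOVA.

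The consequence is limited. Efficacy is exploratory here and no confirmatory test is at risk. What suffers is the precision, and possibly the representativeness, of the effect sizes to be ranked. The change should be made because it costs almost nothing and baseline is already collected for every measure.

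**What to change.** Replace repeated measures ANOVA by a likelihood-based mixed model for repeated measures:

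- **Outcomes:** week 6 and weeks 12–14.
- **Terms:** the baseline value of the same measure as covariate, arm, visit, arm-by-visit and baseline-by-visit. A model with a constrained common baseline mean is an acceptable alternative and also yields within-arm change.
- **Covariance and inference:** unstructured covariance (three parameters for two visits) and Kenward-Roger degrees of freedom.
- **Population:** all randomised children with any post-baseline value, analysed as randomised.
- **Effect size:** adjusted differences divided by the pooled baseline SD of each measure, with 95% intervals. The residual SD should not be used, because the ranking would then depend on how strongly each measure correlates with its own baseline.
- **Change:** within-arm change kept as a descriptive summary, since sensitivity to change is a stated aim.
- **School attendance:** ANCOVA at weeks 12–14 with baseline attendance as covariate.

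The cost is wording, slightly more analysis work and a few degrees of freedom; no new data are needed. One limitation remains: responders will still differ between measures, so the number contributing to each effect size should be shown beside it in the ranking.
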